# Fax: [name]

# [contact]

**study synopsis**

| **TITLE** | | Effects of adalimumab (Humira®) on biomarkers in skin and synovial tissue in patients with psoriatic arthritis |
| --- | --- | --- |
| **STUDY SITE** | | Division of Clinical Immunology and Rheumatology  Department of Dermatology  Academic Medical Center, Amsterdam, The Netherlands |
| PHASE | | 4 |
| **INDICATION** | | Psoriatic arthritis |
| **STUDY OBJECTIVES** | | The primary objective is to study changes in synovial and skin inflammation and cytokine expression in serial biopsy samples following administration of adalimumab therapy to subjects with active psoriatic arthritis.  The secondary objectives of this study are to (i) assess clinical response (ii) compare immunohistochemical analysis and Polymerase Chain Reaction (PCR) analysis of cytokines in tissue samples (iii) to assess changes in gene expression in synovial and skin tissue by microarray analysis (iv) to assess changes in serum biomarkers |
| **MEDICATION** | Adalimumab or placebo for 4 weeks followed by an open label extension study for in total 12 weeks. | |
| **DESIGN** | | Single centre, double-blind, randomized, placebo-controlled study in subjects with clinically active psoriatic arthritis who have have persistent disease activity during treatment with methotrexate (MTX) and who are on stable MTX treatment. Synovial and skin biopsies will be obtained before and after 4 weeks of treatment with adalimumab subcutaneously. |
| **POPULATION** | | Males and females with a diagnosis of psoriatic arthritis |
| **SAMPLE SIZE** | | 24 patients |
| **SAFETY VARIABLES** | | Physical examination, vital signs, adverse events, standard hematology and clinical chemistry laboratory, urinalysis. Chest X-ray, PPD and -HCG pregnancy test (for women) will be performed at screening |
| EFFICACY VARIABLES | | Immunohistologic studies of synovium from an affected joint; immunohistologic studies on skin biopsies of lesional skin; exploratory studies using Q-PCR and microarray analysis; psoriasis area and severity index; body surface area percentage; tender joint score and swollen joint score (based on 68 joints); patient pain score VAS; patient disease activity VAS; physician global assessment of PsA disease activity; CRP, ESR |

| **schedule of assessments** | | | | |
| --- | --- | --- | --- | --- |
|  | screening (-2 weeks) | baseline (week 0) | week 4 | week 12 |
| medical history | X |  |  |  |
| physical examination | X |  |  | X |
| vital signs | X |  |  |  |
| Hematology | X | X | X | X |
| Chemistry | X | X | X | X |
| urinalysis | X | X | X | X |
| chest X ray | X |  |  |  |
| PPD skin test | X |  |  |  |
| serologic test (HIV, HBV, HCV) | X |  |  |  |
| rheumatoid factor | X |  |  |  |
| Anti-CCP antibodies | X |  |  |  |
| Serum for future proteomics |  | X | X | X |
| serum b-hcg | X |  |  |  |
| joint score | X | X | X | X |
| HAQ/VAS | X | X | X | X |
| PASI/BSA | X | X | X | X |
| synovial biopsy |  | X | X |  |
| skin biopsy |  | X | X |  |
| PBMCs |  | X | X |  |
| adverse events |  | X | X | X |
| concomitant medication | X | X | X | X |

APPENDIX 3 Tender joint count, swollen joint count

APPENDIX 4 Standard Operating Procedure biopsy handling

APPENDIX 5 Psoriasis Area and Severity Index (PASI)

**1. INTRODUCTION**

**Psoriatic arthritis and treatment**

Psoriatic arthritis (PsA) occurs in up to 30% patients with psoriasis [1] and is a common chronic rheumatic disease that may result in considerable joint damage if left untreated [2]. Early aggressive treatment is indicated in patients with significant joint inflammation. Conventional therapeutic regimens with disease modifying anti-rheumatic drugs (DMARDs) in psoriatic arthritis are often based on clinical experience or extrapolated data from studies in rheumatoid arthritis (RA), rather than clinical trial evidence in PsA. Currently, sulphasalazine, methotrexate, and leflunomide are considered to be the DMARDs of choice for arthritis in PsA, but the clinical benefit of these DMARDs is marginal to modest [3]. In PsA patients a high concentration of TNF-, a proinflammatory cytokine, is present in synovial fluid and synovial tissue, as well as in psoriatic skin [4-6]. TNF- has proven to be an effective new target for therapy in both psoriasis and PsA [7] .

Our previous work has shown that anti-TNF therapy induces marked beneficial changes at the site of inflammation early after initiation of treatment, both in RA [8,9] and in psoriatic arthritis [10,11].

##### Synovial and skin biopsy in clinical trials

There has been great interest in synovial tissue for the evaluation of disease activity in several forms of arthritis, especially in the research aimed at the development of new treatments. Improvement of the techniques has made the synovial biopsy a safe and uncomplicated procedure, which can be done under local anesthesia in the outpatient clinic [12]. Using a (mini-)arthroscopy sites of active and non-active inflammation can be discriminated and adequate tissue can be obtained in nearly all cases.

Synovial biopsies can be used to evaluate the mode of action of treatment in relation to treatment response using a variety of techniques [13]. Analysis of synovial biopsies for the expression of several markers (e.g. to quantify the cellular infiltrate, pro-inflammatory cytokines, adhesion molecules) The laboratory of the Division of Clinical Immunology and Rheumatology of the Academic Medical Center, has extensive experience with these techniques and has developed an elaborate quality control system for clinical trials, immunohistologic analysis, and computer-assisted digital image analysis [14-16].

Similarly, skin biopsies can be obtained easily under local anesthesia from a psoriatic plaque and can be used to evaluate changes in histologic and immunohistochemical features. Of specific interest will be the assessment of the phenotype of T cells and other inflammatory cells. There is extensive experience with these techniques at the Department of Dermatology of the Academic Medical Center and both departments have a longstanding collaboration in the evaluation of the effects of targeted therapies in patients with psoriasis and psoriatic arthritis [10,11,17,18].

**Examination of the tissue response to treatment to predict clinical effects.**

It can be anticipated that rapid developments in immunology, molecular biology, and biotechnology will lead to a dramatic increase in the number of new, targeted therapies. Therefore, there is a clear need for biomarkers, which could be used for selection purposes during the development process. Examination of serial synovial samples has been proposed as a method that can be used to predict a potential effect of novel antirheumatic interventions [19]. Successful treatment with corticosteroids as well as DMARDs, such as gold, methotrexate and leflunomide, is associated with decreased mononuclear cell infiltration. Similarly, successful treatment of RA subjects with for infliximab and etanercept results in reduced synovial inflammation [13-15]. The effects of adalimumab have not been studied previously.

Of importance is the fact that analysis of serial synovial samples from RA subjects who received either placebo or unsuccessful treatment with recombinant human interleukin-10, IFN-beta, and anti-CD4 antibodies did not reveal significant changes in key synovial biomarkers [15,20-22]. Similarly, there was no clear-cut change in serial biopsies after treatment with IL-1 receptor antagonist at 30 mg/day [23], which appears to have very limited effects on arthritis activity. Taken together, these studies indicate that analysis of serial biopsies can be used as a screening method to test new compounds requiring relatively small numbers of subjects. The absence of changes after treatment would suggest that the therapy is probably not effective. This approach has recently been successful in the evaluation of effects of novel therapeutic strategies for RA, but has as yet not been systematically validated in psoriatic arthritis.

# 2. STUDY OBJECTIVES

**Primary objective**

The primary objective is to study changes in synovial and skin inflammation and cytokine expression in serial biopsy samples following administration of adalimumab therapy to subjects with active psoriatic arthritis.

# Secondary objectives

The secondary objectives of this study are to (i) assess clinical response (ii) compare immunohistochemical analysis and Polymerase Chain Reaction (PCR) analysis of cytokines in tissue samples (iii) to assess changes in gene expression in synovial and skin tissue by microarray analysis (iv) to assess changes in serum biomarkers

# 3. INVESTIGATIONAL PLAN

## **Study medication and dosage**

## Trade name: Humira or matching placebo

Dosage: 40 mg every other week by subcutaneous injection

The study medication will be supplied by the sponsor of this study for the first 4 weeks (first 2 injections).

The investigators will administer/dispense the study medication only to patients included in this study following the procedures set out in the study protocol.

## **Design**

Following a screening period of 2 weeks, patients with active PsA will be enrolled into a (1 : 1) 4-week randomized double-blind, placebo-controlled treatment period. After the second biopsy (at 4 weeks), all patients will receive adalimumab (Humira). Patients are allowed to use concomitant NSAIDs, corticosteroids (prednisone equivalent ≤ 10 mg/day) and methotrexate, provided the dose has been stable for at least 4 weeks prior to baseline.

Biopsies of one target skin lesion will be obtained before administration (preferable from a sun-protected area) of study drug at baseline, and after 4 weeks of treatment (a total of 4 skin biopsies). Synovial biopsies of a clinically inflamed joint (knee, wrist or ankle) will be obtained by arthroscopy before administration of study drug and after 4 weeks of treatment (a total of 2 synovial biopsies). The baseline visit and first arthroscopy *must* be within 3 days before the first administration of study medication. After 4 weeks the arthroscopy will be repeated in the same joint.

A clinical evaluation of both joint and skin symptoms will be repeated after 4 and 12 weeks of treatment. Patients will be seen for efficacy and safety assessments in accordance with standard guidelines for clinical practice during the entire study.

In total there will be 4 study visits: screening, baseline, week 4 and week 12.

There will be a ± 3-day deviation for all return visits. All visits will be fixed with reference to the baseline visit.

### **Statistical basis for sample size**

Only limited knowledge exists on the primary variables used in this study, i.e. the immunohistochemical changes in synovial tissue and skin. Therefore, a formal estimate of the sample size is not possible. Twenty-four male and female subjects with psoriatic arthritis will be recruited to the study, based on our previous experience in comparable studies in RA [14,15] and psoriatic arthritis [10,11,17,18]. The number of subjects is based upon the desire to gain adequate information, while exposing as few subjects as possible to study procedures. Information gained from this study will be used to power future studies.

# Patient identification

All patients must be identifiable throughout the study, even during the run‑in phase (screening to baseline). Therefore, each patient entering the study at screening visit will be assigned a *screening number* (A-01, A-02, A-03, A-04, etc.). Patients will be numbered consecutively; the first patient being screened will receive number A-01, the second patient A-02 and so on. The results of screening procedures will be recorded under this screening-number. On completion of the run‑in phase, all eligible patients will receive a treatment number, a number that might not be identical with the screening number.

Example:

screening number treatment number

subject 1 A-01 B-01

subject 2 A-02 B-02

subject 3 A-03 (not eligible)

subject 4 A-04 B-03

subject 5 A-05 B-04

Patients who are withdrawn from the study for whatever reason will be replaced. Patient screening will be stopped when a total of 24 patients has entered the study.

### **Duration of study**

Duration of the study for the individual subject will be 12 weeks, preceded by a screening period of 2 weeks. The study will be finished after 12 weeks of treatment. Patients who respond well to therapy will be allowed to continue treatment with Humira in a normal outpatient setting with their own rheumatologist.

## **Selection of study patients**

A patient may be enrolled in this study provided that he/she has met all of the inclusion criteria and none of the exclusion criteria. The patients with a diagnosis of active psoriatic arthritis will be recruited at the Division of Clinical Immunology and Rheumatology and the Department of Dermatology of the Academic Medical Center in Amsterdam.

### Inclusion criteria

1. Prior to any study procedure, voluntary written informed consent must be obtained, after the nature and purpose of this study are explained
2. Patients should be between 18 and 80 years of age
3. Patients have presence of active cutaneous lesions of psoriasis or documented history of psoriasis diagnosed by a dermatologist
4. Patients must have a diagnosis of psoriatic arthritis for at least 3 months. The disease must be moderate to severely active as defined by  2 swollen and  2 tender or painful joints
5. If female, patient should either be of not-childbearing potential (i.e. postmenopausal or surgically sterile) or practice a reliable method of birth control until 150 days post-study (e.g. use of condom, IUD, oral contraceptives) or have a vasectomized partner
6. Patients should have inadequate response to NSAID therapy
7. The use of concomitant NSAIDs and corticosteroids is allowed. The dose of corticosteroids should not exceed a prednisone equivalent ≤ 10 mg/day and must be stable for at least 4 weeks prior to baseline
8. The use of concomitant methotrexate (MTX) is allowed. If using MTX, patients must have received a minimum of 3 months of therapy and be on a stable dose for at least 4 weeks prior to baseline
9. Patients are considered to be in generally good health based upon the result of a medical history, physical examination, laboratory profile, chest X-ray and ECG

### Exclusion criteria

Patients will be considered ineligible for study participation is any of the following criteria are met:

1. Patient has previously received anti-TNF therapy, or another investigational drug for psoriasis or psoriatic arthritis **in the past 2 months**
2. Patient has received any DMARD or systemic psoriasis therapy (other than MTX) within 4 weeks prior to baseline
3. Patient has received an intra-articular injection with corticosteroids within 4 weeks prior to baseline
4. Patient has an active skin or connective tissue disease (other than psoriasis and psoriatic arthritis) that would interfere with the assessment of either psoriasis or arthritis
5. Patient has received topical psoriasis therapy (e.g. corticosteroids, vitamin D analogues, keratolytics, coal tar or topical retinoids) within 2 weeks prior to baseline

NB: low potency topical steroids to be used for scalp, palms, groin and/or soles of feet only are allowed

1. Patients has a history of active tuberculosis. A PPD test and chest X-ray done at screening should be negative (in case of latent tuberculosis, a patient may enter the study if prophylaxis with isoniazide is begun prior to administration of adalimumab)
2. Patients has a recent history of (or persistent) infection requiring hospitalization or antibiotic treatment within 4 weeks of baseline
3. Patient is HIV positive. A HIV test done at screening has to be negative
4. Patient has evidence of a hepatitis B or hepatitis C virus infection. A serologic test for HBV and HCV done at screening has to be negative
5. Patient has a significant history of cardiac, renal, neurological, metabolic or any other disease that may affect his/her participation in this study
6. Patient has a history of malignancy (other than basal cell carcinoma of the skin) in the past 10 years
7. If female, patient should not be pregnant or breast-feeding. A serum pregnancy-test will be performed at screening has to be negative
8. Patient is, in the opinion of the investigator, unable to comply with the requirements of the study protocol or is unsuitable for the study for any reason

Any patient who does fulfill the inclusion criteria at screening, but not at baseline may be screened again, and if inclusion criteria are met, enter the study.

### Withdrawal and replacement of patients

Patients may be withdrawn for the following reasons:

- at their own request
- at the discretion of the investigator

Patients must be withdrawn under the following circumstances:

- in case of any intercurrent illness or adverse event, that interferes with the safety of continuous administration of study-drug to the patient

In all cases, the reasons why patients are withdrawn must be recorded in detail in the patient's medical records and the CRF. Patients that leave the study or are withdrawn from the study before week 4 will be replaced.

## **Variables and schedule of assessments**

The following will be determined in accordance with the "Schedule of assessments".

### Background information

At the screening visit of the study, all patients will undergo a full physi­cal examination, and the relevant medical history will be taken. Further to this demographic data will be collected/measured and documented.

The following data will be documented:

. date of obtaining informed consent

. initials, date of birth, sex, race, height, weight

. alcohol consumption/smoking habits

. concomitant illnesses

. concomitant medication

. psoriatic arthritis disease status and time since diagnosis

. prior DMARD history

. relevant findings in physical examination

### Efficacy variables

#### *1. Primary variables*

Primary variables will include the analysis of the cell infiltrate and the expression of cytokines. At baseline an arthroscopy with synovial biopsies of an inflamed joint (knee, wrist or ankle) will be performed. The arthroscopy and biopsies will be repeated in the same joint 4 weeks after first administration of the study drug and before the third injection. Immunohistochemical staining will be performed and analyzed by digital image analysis, as we have previously described and validated for synovial tissue [16].

Initially scores will be obtained for each of the following items:

1. for analysis of the cellular infiltrate:

- CD3 (T-cell marker)
- CD4
- CD8
- CD22 (B-cell marker)
- CD68 (macrophages)
- CD163
- MRP8
- MRP14
- CD38 (plasma cells)
- CD55 (fibroblast like synoviocytes)
- granzyme B (cytotoxic cells)
- CD15

1. for analysis of cytokine expression:

- IL-1
- IL-6
- TNF-

1. for analysis of MMP expression:

- MMP-1
- MMP-3
- MMP-13

1. for analysis of vascularity

- Factor VIII

e) Tissue samples will be stored for future microarray analysis

In addition, PBMCs will be collected before treatment and 4 weeks after the initiation, and serum will be collected before treatment and 4 and 12 weeks after the initiation to determine changes in biological markers.

*2. Secondary efficacy variables*

Secondary variables will consist of:

- Skin biopsies (in total 4x 4 mm punch biopsies) will be performed at baseline and 4 weeks after first administration of study drug from the same lesion. 2 adjacent biopsies will be obtained at each time point from the edge of an active lesion. One of the biopsies will be embedded in tissue-tek before the freezing process for cryosectioning. The other biopsy will be placed in a cryotube and directly frozen in liquid nitrogen for possible PCR or microarray analysis in the future.

The following analysis will be performed:

a) epidermal thickness and morphology

1. assessment of T cells and their activity:

-CD3 (T cell marker)

-CD25 (T cell marker)

1. other inflammatory cells:
   - CD15 (neutrophil marker)
   - CD68 (macrophage marker)
   - CD83 or DC-LAMP (dendritic cell markers)
2. proinflammatory cytokines

- TNF-
- IFN-γ
- The clinical severity of the skin lesions during treatment will be evaluated at each visit using the following parameters:

- Psoriasis Area and Severity Index (PASI) (see appendix)

- total affected Body Surface Area (BSA)

- The clinical severity of the affected joints during treatment will be evaluated at each visit using the following parameters:

-Tender joint count (see appendix)

- Swollen joint count (see appendix)

-Visual Analogue Scale (VAS) pain (see appendix)

-VAS disease activity (see appendix)

-CRP and ESR

-Health Assessment Questionnaire (see appendix)

-Physician’s Global Assessment of Disease (see appendix)

-Patient’s Global Assessment of Disease (see appendix)

### Safety variables

#### *1. Laboratory variables*

HEMATOLOGY: hemoglobin, white blood cell count, platelet count, ESR

chemistry: creatinine, alkaline phosphatase, ASAT, ALAT, LDH, CRP

URINALYSIS: urine dipstick

The following laboratory variables will be assessed at screening only:

- Chest X ray

- PPD skin test

- Virology: tests for HIV, HCV and HBV

- Pregnancy test: serum -hcg in women of child-bearing potential

- Rheumatoid factor, anti-CCP

In this study per patient a total volume of approximately 70-ml of blood will be drawn for study purposes over a period of 14 weeks.

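### The only scheduled pregnancy test is at screening, 14 to 17 days before the first injection and about 6 weeks before the placebo arm first receives adalimumab

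*Protocol*

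**What the plan says.** Four places in the protocol fix one serum hCG test, at screening:

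- Safety variables, Laboratory variables: the pregnancy test is in the list headed "The following laboratory variables will be assessed at screening only".
- Study synopsis, safety variables: the "pregnancy test (for women) will be performed at screening".
- Schedule of assessments: the hCG row has one mark, under screening. Baseline, week 4 and week 12 are blank.
- Exclusion criteria: "A serum pregnancy-test will be performed at screening has to be negative".

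The dosing timeline comes mainly from the Design section. It begins "Following a screening period of 2 weeks, patients with active PsA will be enrolled", and the baseline visit must "be within 3 days before the first administration of study medication". After the second biopsy every patient receives adalimumab, so for the placebo arm that is the first exposure. Primary variables sets the second biopsy at "4 weeks after first administration of the study drug and before the third injection". The visit window in Design is a "3-day deviation for all return visits. All visits will be fixed with reference to the baseline visit".

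The protocol treats pregnancy as a reason to withhold the drug. It is an exclusion criterion, and the inclusion criteria require non-child-bearing status, reliable contraception until 150 days post-study, or a vasectomised partner.

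**The concern.** A test meant to keep the drug from pregnant women protects best when it sits close to the first dose. Here it is about two weeks early for the adalimumab arm and about six weeks early for the placebo arm, which is half the patients under 1:1 allocation. A pregnancy that begins after screening, or that was too early to detect then, would not be picked up by any scheduled test before adalimumab is first given in either arm.

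What is at stake is patient safety only. The point does not bear on the treatment comparison, the sample size or any error rate.

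**Working it through.** The protocol states no interval from test to dose, so there is no figure to reproduce. The intervals follow by counting days on its schedule.

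**Inputs from the protocol**
- Screening: 14 days before baseline (schedule of assessments; Design).
- Baseline visit to first injection: 0 to 3 days (Design).
- Second biopsy: 28 days after first administration (Primary variables).
- Visit window: ±3 days on return visits (Design).

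**Interval from the hCG test to the first injection**
- Nominal: 14 + (0 to 3) = 14 to 17 days.
- If the ±3-day window is also applied to the screening-to-baseline interval, which the text does not clearly say: 11 to 20 days.

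**Interval from the hCG test to the placebo arm's first adalimumab**
- Counting week 4 from first administration: 14 + (0 to 3) + 28 = 42 to 45 days (6.0 to 6.4 weeks). With ±3 days at week 4: 39 to 48 days (5.6 to 6.9 weeks).
- Counting week 4 from the baseline visit, as Design does for visits: 14 + 28 = 42 days, or 39 to 45 with the window.
- If the window also applies to screening-to-baseline, the first reading widens to 36 to 51 days.
- The upper end is not truly fixed, because the open-label dose is only placed after the biopsy.

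**If a test were added at baseline only**
- Placebo arm: (0 to 3) + 28 = 28 to 31 days, or 25 to 34 with the window. A week 4 test is therefore needed as well.

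**Expected number of conceptions in the gap.** Two assumptions are not in the protocol: 10% to 40% of the 24 patients are women of child-bearing potential, and annual contraceptive failure is 1% to 10%.
- Women of child-bearing potential: 0.10 × 24 = 2.4 to 0.40 × 24 = 9.6, that is 1.2 to 4.8 per arm of 12.
- Formula per arm: women × annual failure rate × days / 365.

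| Arm | Low | High |
|---|---|---|
| Adalimumab, 14 to 17 days | 1.2 × 0.01 × 14/365 = 0.0005 | 4.8 × 0.10 × 17/365 = 0.022 |
| Placebo, 42 to 45 days | 1.2 × 0.01 × 42/365 = 0.0014 | 4.8 × 0.10 × 45/365 = 0.059 |
| Sum, nominal | 0.0018 | 0.082 |
| Sum, windows (11 to 20; 39 to 48) | 0.0016 | 0.089 |
| Sum, widest (11 to 20; 36 to 51) | 0.0015 | 0.093 |

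Every reading is below 0.1 for the whole trial. Conceptions too early to detect at screening would add to these figures.

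**Is a repeat test ordered anywhere else?** Urinalysis is done at every visit but is described only as a dipstick. Medical history is scheduled at screening only, and physical examination at screening and week 12 only, so neither falls on the two visits that precede first adalimumab. The provision for re-screening at baseline names the inclusion criteria, while pregnancy is an exclusion criterion. No eligibility check is stated before the open-label dose.

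**The case against.** The strongest reply is that nothing is misstated. Four sections fix the same rule coherently, and none promises a later test, so the complaint may amount to preferring a denser schedule. The protocol's continuing control is contraception, and the proposed fix relies on it too: it adds no test after week 4, although treatment runs to week 12.

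Other provisions also help. Eligible patients receive a treatment number only when the run-in is complete, which suggests eligibility is settled then. Concomitant medication is recorded at each visit, the investigator may withdraw patients, and safety assessment follows routine practice throughout, so a test on clinical suspicion is always possible. The sponsor supplies drug only for the first two injections, so what is checked before open-label dispensing cannot be fully judged from this document. The intervals shift by a few days with the reading of the window, and the expected count rests on outside assumptions.

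Most of this stands as mitigation, and it limits the weight of the point. It does not answer it: contraception lowers the risk but detects nothing, and none of these provisions orders a test before either first exposure. The choice of reading does not alter the conclusion of roughly two and six weeks.

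**Conclusion.** The concern holds as a minor, optional safety improvement. The protocol is consistent, but its rule leaves no scheduled pregnancy test between screening and first adalimumab: nominally 14 to 17 days in the adalimumab arm and 42 to 45 days in the placebo arm (39 to 48 with the visit window). These intervals rest on the protocol alone.

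The expected number of affected pregnancies, about 0.002 to 0.09, rests wholly on the assumed share of women of child-bearing potential and the assumed contraceptive failure rate. The protocol gives no fetal-risk figure, so harm per event is not quantified. The case for acting is that the protocol already sets out to prevent this exposure, and that the change is cheap.

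**What to change.** For women of child-bearing potential, add an hCG test at baseline and at week 4 to the schedule of assessments, on blood or urine already collected at those visits (Methods of investigation). Require a negative result before the first injection and before the first open-label adalimumab dose. Take the pregnancy test out of the screening-only list under Laboratory variables, and align the exclusion criterion and the synopsis.

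The interval from last test to first adalimumab then falls to 0 to 3 days in the adalimumab arm. In the placebo arm it becomes the gap between the week 4 visit and the first open-label dose. Testing all such women at both visits needs no knowledge of allocation, so the blind is not threatened.

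The cost is about 2 to 10 assays per time point (2 × 2.4 = 4.8 to 2 × 9.6 = 19.2 in total, under the same assumption), with no extra visit, staff or invasive procedure. The result must be available before dosing, so a rapid urine test would be needed if the first injection is given on the day of the baseline visit. A conception in the few days before a test would still be missed.
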